**Methods/design:**

This double-blind randomized controlled trial will enroll 60 elderly patients (60–85 years) meeting ICSD-3 criteria for CI and Rome IV criteria for FD. Using block randomization with computer-generated sequences, eligible participants will be allocated 1:1 to either active taVNS group (*n* = 30) or sham control group (*n* = 30). The CFDA-certified transcutaneous vagus nerve stimulator (Model tVNS501, Reach Medical, China; Registration No. SuXieZhun20212090050) will be positioned at standardized anatomical sites: the concha cymba (the inferior margin of the intersection between the superior and inferior crura of the antihelix within the cymba conchae), electrical stimulation will deliver with fixed parameters (frequency: 80 Hz, pulse width: 100 μs, pulse 40–60s). The active group will receive validated taVNS parameters, while the sham group will undergo identical procedures without electrical output. Interventions will be administered 30 min per session, 5 sessions weekly for 3 consecutive weeks. Primary endpoints include changes in Pittsburgh Sleep Quality Index (PSQI) and Nepean Dyspepsia Symptom Index (NDSI) at week 3. Secondary outcomes encompass Insomnia Severity Index (ISI), 36-Item Short Form Survey (SF-36), and serum biomarkers (pro-inflammatory cytokines IL-1*β*, IL-4, IL-6, TNF-*α*, hs-CRP, TGF-β; neurotransmitters Dopamine (DA), serotonin (5-hydroxytryptamine, 5-HT), norepinephrine (NE), Glutamate (Glu), *γ*-aminobutyric acid (GABA)). Safety profiles will be systematically evaluated using CTCAE v5.0 criteria, with all adverse events documented throughout the study.

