### Sample size estimation

2.5

Based on existing RCT literature, the efficacy rate of taVNS in treating elderly patients with CI ranges from 73.3 to 93.3% (21, 22), while its efficacy in FD reaches 92.3% (3). Building upon our preliminary exploratory clinical study involving 10 cases, we observed an 80.0% efficacy rate (*p* < 0.01) for taVNS in treating elderly patients with CI comorbid with FD, demonstrating significant clinical effectiveness.

This study employed a superiority trial design and utilized PASS 2021 software (NCSS LLC, Kaysville, USA) for prospective sample size estimation. Based on clinical data reported in reference (23), with anticipated efficacy rates of 20% in the sham stimulation group and 70% in the active stimulation group, we conducted a two-independent proportion *z*-test analysis with the following parameters: type I error probability *α* = 0.05, statistical power 1-*β* = 0.99, and 1:1 allocation ratio. Through Monte Carlo simulation validation, the minimum theoretical sample size was calculated as 28 participants per group.

In accordance with CONSORT Statement guidelines regarding dropout rates and considering our institutional clinical practice experience with anticipated 5–10% dropout rates, we ultimately determined to enroll 30 participants per group (total *N* = 60). This sample size enables detection of a Cohen’s *h* effect size of 0.99 (Power = 0.991, 95% CI 0.89–1.07), satisfying the statistical power requirements for superiority trials.

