### Randomization and blinding

2.6

The randomized controlled trial (RCT) utilized a simple randomization method implemented via the PROC PLAN procedure in SAS 9.4 software, which was designed by an independent statistician. A fixed seed number of 60 was preset to ensure reproducibility, and participants were allocated to the two groups (30 each) at a 1:1 ratio, with random numbering from 01 to 60, generating 60 unique sequences to ensure unbiased group allocation. The group allocation information was sealed in tamper-evident opaque envelopes and managed by a blinded study coordinator who was not involved in participant recruitment or outcome assessment, ensuring strict allocation concealment.

During trial execution, consecutively enrolled participants meeting inclusion criteria were sequentially assigned unique identification numbers. The blinded trial coordinator strictly adhered to the enrollment chronology when unsealing pre-sequenced, tamper-evident sealed envelopes. The revealed allocation information was subsequently transferred to an independent investigator uninvolved in recruitment or intervention delivery, who executed group assignments per the predefined randomization matrix. The study protocol explicitly prohibited any deviation from allocation sequences or non-programmatic modifications.

The independent researcher, based on randomized allocation, preset the transcutaneous auricular vagus nerve stimulator (tVNS501) with fixed parameters (intensity: 20–40 mA, frequency: 80 Hz, pulse width: 100 μs, pulse 40–60s) and blinded the display screen using opaque tape before handing it to a clinical operator. In the active stimulation group, the device was powered to deliver real stimulation, while in the sham stimulation group, the device remained inactive (no current output) but maintained physical contact. A triple-blind design (participant-operator-outcome assessor) was implemented throughout the study to maintain blinding of group assignment (taVNS or sham taVNS). Unblinding was performed post-database lock by an independent statistician using SAS 9.4 (SAS Institute Inc., Cary, NC), strictly adhering to the predefined protocol. This study strictly adhered to the principle of observer independence in clinical research (Figure 1).

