##### Pittsburgh sleep quality index (PSQI)

2.8.2.1

Assessment timepoints: Baseline (T0), post-intervention (T1, week 3), and follow-up (T2, week 4 post-treatment).

Evaluation domains: Seven components including subjective sleep quality, sleep latency, and sleep duration.

Scoring system: Total scores range from 0 to 21, with ≥8 indicating sleep disturbance. A change ≥3 points was considered clinically significant.

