After de-identified data underwent ETL (Extract-Transform-Load) processing for standardization, the standardized data were imported into statistical software for further analysis. Measurement data were expressed as Mean ± SD. Differences among groups were analyzed by Student *t* test or one-way ANOVA, SNK or LSD method was used for multiple comparison. Qualitative data were described as percentages and analyzed using Chi-square (*χ*^2^) test or Fisher’s exact test as indicated. The *p*-value reported was two-sided and value of less than 0.05 was considered statistically significant. All analyses were performed using the SPSS software (Version 20.0, SPSS Inc., USA).

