#### Control of confounding bias

2.11.2

Confounding bias predominantly arises during data analysis due to distorted causal relationships between exposure factors and outcome variables. When confounding factors (third variables associated with both exposure and outcome) remain inadequately adjusted, erroneous causal attribution may occur, leading to overestimation or underestimation of effect sizes. This study implemented multivariable regression models (adjusting for baseline covariates such as age and gender) combined with propensity score matching to statistically control known confounders.

Additionally, sensitivity analyses were conducted to assess potential impacts of unmeasured confounders, with *E*-values quantifying the robustness of causal inferences. A prospective covariate data collection protocol (based on literature review and causal diagram analysis) further ensured systematic identification of confounding factors.

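### Two-arm efficacy analysis: an unadjusted t-test with post-hoc procedures that have nothing to compare, and a second analysis with propensity matching whose role is undefined; one baseline-adjusted ANCOVA per primary score should replace both

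*Protocol article*

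**What the plan says.** **Design.** Section 2.6 of the protocol article states that "participants were allocated to the two groups (30 each) at a 1:1 ratio". The abstract sets the target: "Primary endpoints include changes in Pittsburgh Sleep Quality Index (PSQI) and Nepean Dyspepsia Symptom Index (NDSI) at week 3". Sections 2.8.2.1 and 2.8.2.2 schedule both scales at T0, T1 and T2, so each participant's baseline score will be on file.

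**Section 2.8.5 (Statistical analysis).** Differences among groups in measurement data are tested by Student t test or "one-way ANOVA, SNK or LSD method was used for multiple comparison". No covariate or model is given. The same section makes the ITT set primary and the per-protocol set a sensitivity analysis.

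**Section 2.11.2 (Control of confounding bias).** The study is said to have used "multivariable regression models (adjusting for baseline covariates such as age and gender) combined with propensity score matching to statistically control known confounders". Sensitivity analyses for unmeasured confounders follow, with E-values. The regression and matching are tied to no outcome and are not labelled primary or supportive.

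**The concern.** Three things do not fit together.

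- SNK and LSD separate several group means after an overall F test. This trial has two groups.
- Propensity matching and E-values are tools for non-randomised comparisons. Here allocation is random, so baseline imbalance is due to chance and confounding by allocation is handled by design. Matching can only remove randomised participants.
- The two sections describe an unadjusted and an adjusted analysis without ranking them, and neither names the baseline value of the scale being analysed, an obvious prognostic covariate.

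At stake are precision in a trial of 60 people, retention of everyone randomised, and certainty before unblinding about which estimate decides each primary score.

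**Working it through.** **The plan's own figure.** Section 2.5 gives 28 per group for 20% against 70%, with "type I error probability *α* = 0.05, statistical power 1-*β* = 0.99, and 1:1 allocation ratio". The unpooled two-sided z-test reproduces it: (1.960 + 2.326)² × (0.2×0.8 + 0.7×0.3) / 0.5² = 18.37 × 0.37 / 0.25 = 27.2, rounded up to 28. This calculation concerns responder rates, so it does not bear on how the mean scores are analysed.

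**SNK/LSD.** With k groups there are k(k−1)/2 pairwise comparisons. For k = 2 that is 1, and one-way ANOVA is then the t-test (F = t²). Nothing is left for a post-hoc procedure.

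**Efficiency.** Inputs from the article: n = 30 per arm, and a two-sided 0.05 level ("value reported was two-sided and value of less than 0.05 was considered statistically significant"). Assumptions, because the article gives no SD or correlation: SD = 1 at both visits, baseline-outcome correlation r from 0.3 to 0.7, and a true effect of 0.6 SD for the power illustration.

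- Variance factor, t-test on change: 2(1 − r)
- Variance factor, ANCOVA on baseline: 1 − r²
- Ratio ANCOVA/change: (1 − r²) / [2(1 − r)] = (1 + r)/2
- Allowing for estimation of the slope, the ANCOVA factor is multiplied by 1 + 1/(2n − 4) = 1 + 1/56 = 1.018
- Power = Φ(0.6/√(2v/n) − 1.96), and detectable difference at 80% power = (1.960 + 0.842)√(2v/n), where v is the variance factor

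| r | (1+r)/2 | saving | ratio with 1.018 | power, change → ANCOVA | detectable difference (SD), change → ANCOVA |
|---|---|---|---|---|---|
| 0.3 | 0.65 | 35% | 0.66 | 50% → 68% | 0.86 → 0.70 |
| 0.5 | 0.75 | 25% | 0.76 | 64% → 76% | 0.72 → 0.63 |
| 0.7 | 0.85 | 15% | 0.87 | 85% → 90% | 0.56 → 0.52 |

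At r = 0.5, 30 per arm under ANCOVA is worth about 30/0.75 = 40 per arm under the change-score t-test, before the small slope correction. A simulation of 3,000 runs per scenario agreed: 50% → 67%, 62% → 74% and 85% → 89%. With no true effect, all methods simulated rejected in about 5% of runs, so the t-test is valid.

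**Matching.** Section 2.11.2 gives no ratio, caliper or algorithm. Assuming 1:1 greedy nearest-neighbour matching with a caliper of 0.2 SD of the logit, on 30 against 30:

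- Age and sex only: one simulation kept 21.7 pairs on average, a second kept 20.8.
- Four covariates: 20.1 pairs. Eight covariates: 18.6 pairs.

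The loss is therefore 30 − 21.7 = 8.3 to 30 − 18.6 = 11.4 pairs. At 0.6 SD, power of a t-test on the week-3 score fell from 63–64% unmatched to 49–50% matched on age and sex.

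**The case against.** Much can be said for the plan, and several stronger readings fail.

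- *A reader might infer that the t-test ignores baseline.* The abstract's endpoint is change, and a t-test on change does use the baseline score. That is why the table takes change as its benchmark. Section 2.8.5 does not say which quantity enters the test. Against the raw week-3 score the saving would be r², that is 9%, 25% and 49%, but that is not the endpoint the article defines.
- *A reader might infer that SNK/LSD is meant across T0, T1 and T2.* That use would ignore within-person correlation. The text speaks of differences among groups, not visits, so this is conditional. On the literal reading the procedures are merely superfluous.
- *A reader might infer a flat contradiction of ITT, or two rival primary results.* Section 2.8.5 fixes ITT as primary, and 2.11.2 sits among the quality-control measures without calling matching primary. The departure arises only if matching is used for efficacy. What the text does show is an undefined role.
- *The adjusted regression is already there.* This stands in part. The covariates in 2.11.2 are given as examples, so baseline scores could be included, but they are not named and the link to 2.8.5 is missing.
- *Matching losses depend on the algorithm.* This stands. Full matching or matching with replacement would behave differently.
- *Detail belongs in an analysis plan.* This is fair for the finer model specification. It does not excuse methods that the article does state and that do not suit the design.

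**Conclusion.** The point holds as one of fit, clarity and efficiency, not of validity. SNK/LSD has no use between two arms. Matching and E-values answer a question that randomisation has already dealt with. Sections 2.8.5 and 2.11.2 leave an unadjusted and an adjusted analysis unreconciled.

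The t-test on change keeps its 5% error rate but gives up 15% to 35% of variance relative to ANCOVA, or roughly 5 to 17 power points at 0.6 SD. The gain shrinks as the correlation rises, and it rests on the assumed range 0.3 to 0.7 with equal SDs at both visits. The matching loss of about 8 to 11 pairs rests on the assumed 1:1 match and caliper, and matters for efficacy only if the matched analysis is used there.

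**What to change.** In 2.8.5, name one primary analysis for each primary score: ANCOVA of the week-3 score on arm, with that scale's own baseline score as covariate. Taking change as the dependent variable in the same model gives the identical arm effect, so the endpoint need not be redefined. Add any stratification factors actually used in randomisation. Section 2.11.1 mentions age and disease severity, whereas 2.6 describes simple randomisation, so establish first which applies.

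Delete SNK/LSD, propensity score matching and E-values. In 2.11.2, either label the age/gender regression a sensitivity analysis or fold those covariates into the primary model, so that the two sections agree.

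The cost is a revision of two sections and, for the baseline covariate, one degree of freedom. No new data are needed. Section 2.6 places unblinding after database lock, and the article does not say whether this has occurred. The change should be made and dated before then if it has not.

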**Discussion:**

This study mitigate the adverse effects associated with the significant side effects of oral medications in elderly patients with CI comorbid with FD. It seeks to scientifically validate the clinical efficacy of taVNS therapy, elucidate its underlying anti-inflammatory and neuromodulatory mechanisms, and establish a multimodal evidence chain integrating “efficacy-inflammation-neuromodulation.” By doing so, this research provides a novel, convenient, scientifically validated, effective, and safe non-pharmacological therapeutic approach for elderly patients with CI and FD, it offers innovative insights and methodologies for the development of pharmaceuticals, medical devices, and related products.

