Currently, pharmacological treatments for CI in the elderly are associated with systemic risks. Studies have shown (11–14) that the risk of dependence on benzodiazepines is 34.7% (OR = 3.2, 95%CI 2.1–4.9), and the incidence of withdrawal syndrome after discontinuation is 28.4% (RR = 2.8). Additionally, a significant dose ineffectiveness threshold effect has been observed, necessitating off-label dosing in some patients, while 12.7% of patients exhibit a decline in estimated glomerular filtration rate (eGFR), and the incidence of hepatorenal toxicity is ≥30%. The treatment of FD lacks targeted therapies and effective drugs, with proton pump inhibitors (PPIs) showing a clinical response rate of only 38.2% (95%CI 32.7–44.1), and long-term use of prokinetic agents increases the risk of QT interval prolongation (HR = 1.68) (15, 16).

When CI and FD coexist, the risk of drug interactions increases by 71% (*p* < 0.001) (17), and the cost-effectiveness ratio of conventional therapies is as high as $152,300 per quality-adjusted life year (QALY) (18). Therefore, there is an urgent need for reliable, safe, cost-effective, and efficient clinical treatment options for elderly patients with CI comorbid with FD. In this context, taVNS emerges as a novel therapeutic approach, offering a potential innovative solution for this patient population.

This study will systematically evaluate the clinical efficacy of transcutaneous auricular vagus nerve stimulation (taVNS) in elderly patients with CI comorbid with FD. By analyzing dynamic fluctuations in inflammatory cytokines and neurotransmitters, we will objectively validate the clinical effectiveness of taVNS in geriatric comorbidity management for the first time. The investigation will further elucidate the vagus nerve-mediated regulatory mechanism of duodenal mucosal inflammation and establish a novel non-pharmacological intervention characterized by precision targeting, high safety profile, and enhanced therapeutic compliance, which will provide a theoretical foundation for developing neuromodulation-based integrated therapeutic strategies for elderly patients with multimorbidity management.

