##### Insomnia severity index (ISI)

2.8.3.1

Assessment timepoints: Consistent with the aforementioned schedule (T0-T2).

Multidimensional assessment: Five clinical dimensions were evaluated, including sleep disturbance severity and daytime functional impairment.

Clinical thresholds: 0–7 (no clinically significant insomnia), 8–14 (subclinical insomnia), 15–21 (moderate-to-severe insomnia).

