##### 36-item short form health survey (SF-36)

2.8.3.2

Assessment timepoints: Consistent with the aforementioned schedule (T0-T2).

Health domains: Eight dimensions including physical functioning (PF) and role limitations due to physical health (RP).

Score transformation: Raw scores were converted to standardized scores (0–100) using the formula: [(Raw score - Minimum possible score)/(Maximum possible score - Minimum possible score)] × 100.

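### Eleven serum biomarkers fall under one unadjusted p<0.05 rule with no lead marker, while the article says they will establish mechanism; label them exploratory

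*Protocol article*

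**What the plan says.** Section 2.8.5 (Statistical analysis) compares groups by t test or ANOVA for continuous data and by chi-square or Fisher tests for categorical data. It then gives a single threshold, with no distinction between primary and secondary outcomes: "The *p*-value reported was two-sided and value of less than 0.05 was considered statistically significant". Its one reference to multiplicity is "test or one-way ANOVA, SNK or LSD method was used for multiple comparison".

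The abstract lists the secondary measures: "Secondary outcomes encompass Insomnia Severity Index (ISI), 36-Item Short Form Survey (SF-36), and serum biomarkers". Section 2.8.3.3 names six inflammatory markers (IL-1β, IL-4, IL-6, TNF-α, hs-CRP, TGF-β). Section 2.8.3.4 names five neurotransmitters (DA, 5-HT, NE, Glu, GABA). Both panels are sampled at baseline and at T1 (week 3) only. Neither section names a lead marker or an order of testing.

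The article's aims for these measures are strongly worded. The abstract's Discussion says that the trial seeks to "elucidate its underlying anti-inflammatory and neuromodulatory mechanisms, and establish a multimodal evidence chain". Section 1 (Background) says: "By analyzing dynamic fluctuations in inflammatory cytokines and neurotransmitters, we will objectively validate the clinical effectiveness of taVNS". Section 3 (Discussion) says that monitoring the markers deciphers the regulatory pathways of the auricular vagus nerve. The closing part of section 3 ties a mechanism conclusion to superiority on both symptom scales and, among the limitations, calls the design exploratory.

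**The concern.** A threshold of 0.05 holds the error rate of one test at 5%. Applied separately to 11 markers, it does not hold the chance of at least one false positive anywhere near 5%. With no marker named in advance, any one that crosses the line can be presented as the anti-inflammatory or neuromodulatory link in the claimed chain of evidence.

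The SNK/LSD wording gives no protection. These procedures compare several group means on one outcome. This trial has two arms, so each outcome has a single between-arm comparison and nothing for them to correct.

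At stake is how far the mechanism claim can be trusted. The comparison on PSQI and NDSI is not touched.

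**Working it through.** The article states no error rate for the biomarker family, so there is no figure of its own to reproduce. The check uses its threshold and its list of markers.

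**Inputs from the article**
- Threshold: two-sided 0.05 (section 2.8.5).
- Markers: 6 inflammatory (2.8.3.3) + 5 neurotransmitters (2.8.3.4) = 11.
- Post-baseline time points for these markers: one (T1), so m = 11 between-arm tests.

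**Assumption**
- Correlation ρ between the test statistics. The article gives none, so a common value is assumed and varied from 0 to 0.8.

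**Step 1: independent tests, no effect on any marker**
P(at least one p<0.05) = 1 − 0.95^m = 1 − 0.95^11 = 1 − 0.569 = 0.431.
Expected number of false positives = 11 × 0.05 = 0.55, at any correlation.

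**Step 2: correlated tests**
Write each statistic as Z_j = √ρ·C + √(1−ρ)·E_j, with C and E_j independent standard normal. Then

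P(at least one) = 1 − ∫ φ(c)·[Φ((1.96 − √ρ·c)/√(1−ρ)) − Φ((−1.96 − √ρ·c)/√(1−ρ))]^m dc.

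Numerical integration agrees with simulation to within about 0.001:

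| Family | ρ = 0 | ρ = 0.5 | ρ = 0.8 |
|---|---|---|---|
| 6 inflammatory markers | 0.26 | 0.21 | 0.14 |
| 5 neurotransmitters | 0.23 | 0.18 | 0.13 |
| All 11 biomarkers | 0.43 | 0.30 | 0.18 |

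At ρ = 0.8 the 11-marker figure is still 0.18/0.05 = 3.6 times the nominal level.

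**Step 3: direction**
The rule is two-sided, and section 2.8.3.3 defines biological significance as a change without giving its direction, so both tails are counted. A stricter reader who counts only the favourable tail gets, for independent tests, 1 − 0.975^11 = 0.243.

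**Step 4: does the condition in section 3 help?**
- taVNS affects neither symptoms nor markers: the condition needs superiority on both scales. Its probability cannot exceed that of one scale alone, at most 0.05. A mechanism conclusion drawn only under this condition is then rare.
- taVNS improves both scales but moves no marker: the condition is met, and if the marker results do not depend on the symptom results, the 0.18 to 0.43 from step 2 remains in full.

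The second case is the one that a mechanism claim has to survive.

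**The case against.** The strongest reply is that this is a journal article. Control of multiplicity across secondary endpoints is usually left to an analysis plan, which is not shown, and a general 0.05 threshold promises nothing about a family of tests. Silence would indeed be no finding. But section 2.8.5 is not silent: it states a rule for all comparisons and names a multiple-comparison method that cannot apply across outcomes, while other sections promise to establish and validate on the strength of these markers.

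A second reply is that section 3 calls the design exploratory and makes its mechanism conclusion conditional on both symptom scales. This stands in part. It would be wrong to say that the article has no exploratory wording, or that roughly one trial in three would meet the section 3 condition by chance when taVNS does nothing. However, the remark is a general limitation attached to no test, section 2.5 describes a superiority trial, and the condition names no biomarker. The statements in the abstract's Discussion, in section 1 and earlier in section 3 carry no such condition.

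A third reply is that no section says one marker at p<0.05 proves mechanism. Section 2.8.3.3 uses a change of more than 15%, and section 2.8.3.4 uses correlations with symptom improvement. That is correct. The point is that the plan leaves the single-marker reading open, not that it prescribes it. Those other criteria are not counted here.

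A reader might infer a larger problem by adding ISI and the eight SF-36 dimensions, which gives 1 + 8 + 11 = 20 measures, or 9 × 2 + 11 = 29 tests over T1 and T2. The article does not support that as evidence about mechanism: ISI and SF-36 are not mechanism measures, and separate tests of each SF-36 dimension, or at both visits, are not stated. Nor does it make a confirmatory quality-of-life claim for this trial; SF-36 is only listed as an outcome.

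**Conclusion.** The concern holds for the 11 serum biomarkers. Under the stated rule, if taVNS moves no marker, the chance of at least one significant marker is about 0.30 at an assumed common correlation of 0.5, within a range of 0.18 (correlation 0.8) to 0.43 (independence). The range rests on the assumed correlations and on one between-arm test per marker at week 3. It is the chance of a stray significant marker, not of a false mechanism conclusion under the condition in section 3. It becomes the relevant figure when symptoms truly improve and no marker moves.

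The mechanism wording is therefore stronger than the stated analysis can bear. This is a cheap improvement to the analysis text and the claims; it does not call the primary comparison into question.

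**What to change.** - In section 2.8.5, limit the p<0.05 significance claim to the primary endpoints at week 3.
- In the same paragraph, state that the inflammatory markers and neurotransmitters, and the other secondary measures, are exploratory and are reported as between-arm estimates with 95% confidence intervals.
- Reword the abstract's Discussion, the aim at the end of section 1, and the mechanism statements in section 3 (including the conditional one near its end) so that mechanism findings are hypothesis-generating.

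The cost is one paragraph and some softer wording, with no added patients, visits or assays. The downside is that a single nominally significant marker can no longer be presented as proof of mechanism.
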